### Sample size

Due to major restructuring of services and staff within the Tusla Child and Family Agency in 2014–2016, our key collaborating site had to withdraw from the research. Thus, our sample size will be smaller (n = 50) than that advised by our sample size calculation that indicated that, factoring in 30 per cent attrition, we would need to recruit 150 families to detect a 0.8 effect size on our primary outcome measures. Given the reduced sample size, the results of this RCT should be interpreted with some caution.

### Measures

A range of psychometrically robust measures will be administered to all participants who agree to take part in the ChARM research programme. These measures have been selected because they are brief and easy-to-complete whilst also providing as comprehensive an assessment as possible of all participating families.
Table 1 and
Table 2 outline the measures used within the RCT, process evaluation and costs analyses. Further details on the outcome measures used are also available in the
Supplementary Material (
Supplementary File 1).

**Table 1. T1:** Measures within the RCT. A list of psychometric and observational measures will be administered as part of the impact evaluation to assess outcomes for families.

Measure	Participant	Objective
Impact evaluation		
Conflict Tactics Scale Parent- Child – Short Form	Parent	Parent-reported incidences of child maltreatment
Strengths and Difficulties Questionnaire adult version	Parent	Parent report of child behaviour and wellbeing: conduct, peer & emotional problems, hyperactivity
Strengths and Difficulties Questionnaire child version	Child 7–10 years	Child report of own behaviour and wellbeing: conduct, peer & emotional problems, hyperactivity
Brief Child Abuse Potential Inventory	Parent	Risk factors for child abuse, e.g. parental distress, rigidity, problems with child, self, family and others
Parenting Stress Index	Parent	Parenting stress and parent-child relationship
HOME SF 3–5/6–10 years	Parent and child	Observation of parent-child interaction in the home
Depression, Anxiety and Stress scale	Parent	Parental depression, anxiety and stress
CAGE	Parent	Screener for alcoholism of parent and partner
Drug Abuse Screening Test	Parent	Drug use of parent and partner
Record of incidence of child maltreatment	Collaborating site	Social work record of incidence of child maltreatment in previous six months
Record of out-of-home placement	Collaborating site	Social work record of incidence of out-of-home placement in previous six months
Profile Questionnaire	Parent	Demographic information on families

**Table 2. T2:** Measures within the process evaluation and economic analyses. The process evaluation will utilize a range of qualitative and quantitative measures to assess programme fidelity and implementation, recruitment of sites and families, participant engagement and experiences, and the feasibility of implementing the programme within child and family services in Ireland not involved in the RCT. Several measures will also be applied in order to conduct a costs analyses of ChARM.

Measure	Participant	Objective
Process evaluation		
Session checklists	Practitioners	Fidelity of program content
Work Alliance Inventory	Practitioners & Parents	Practitioner-parent relationships
IY Agency Implementation Effectiveness Questionnaire	Practitioners & managers	Site and practitioner capacity to implement the program with integrity
In-depth semi-structured interviews	Practitioner & managers	Assess experiences of developing, coordinating and implementing program
Records of meetings	Research team	Assess experiences of recruiting sites, developing and implementing program
Attendance records	Practitioners	Records of parental attendance to program
PLSP feedback form	Parent	Parental feedback on Positive Life Skills Program
Home visits feedback form	Parent	Parental feedback on home visits
IY parent satisfaction questionnaire	Parent	Parental feedback on Incredible Years parenting program
Working Alliance Inventory	Parent	Parent-practitioner relationship
Semi-structured interview for parents (including attritors)	Parent	Assess experiences of participating in the program
Draw and Tell interview	Child 7–11 years	Experiences of child wellbeing and family
Cantril’s ladder	Child 7–11 years	Life satisfaction on 1–10 scale of ladder
My family and me	Child 7–11 years	Emotional closeness of family relationships
Semi structured interview/focus group	Child and Family services	Assess feasibility of implementing the ChARM program within current systems of care in Ireland
Economic analyses		
Costs diaries for program inputs	Practitioners & managers	Estimate the cost per family of delivering the program
Service Utilisation Questionnaire	Parent	Document health, educational and social services used by families in previous six months

***RCT***

The trial has two primary outcomes:

Parent-reported incidences of child maltreatment, assessed with The Conflict Tactics Scales Parent-Child – Short Form Amended (CTSPC – SFA) (
Straus *et al.*, 1998). The CTSPC-SFA measures incidences of psychological aggression, neglect and non-violent discipline, and threats of corporal punishment. The parent will complete the CTSPC-SF for a chosen index child and sibling.Child behaviour and wellbeing, assessed using both the parent- and child-report versions of the Strengths and Difficulties Questionnaire (SDQ) (
Goodman, 1997). The SDQ assesses child conduct problems, hyperactivity, emotional symptoms, peer problems, and pro-social behaviour among 3–17 year olds. Parents will complete the SDQ for a chosen index child. The child-report version of the SDQ is appropriate for administration to children seven years and above; therefore, it is will be administered to a subsample of children within this study, i.e. children aged 7–10 years (
Di Riso *et al.*, 2010).

Secondary outcomes are:

Risk factors for child abuse (Brief Child Abuse Potential Inventory [BCAPI]: parent report;
Ondersma *et al.*, 2005);Parenting stress and parent-child interaction (Parenting Stress Index – Short Form [PSI-SF]: parent report;
Abidin, 1995);Observation of parent-child relationship in the home environment (Home Observation for Measurement of the Environment Short Form [HOME-SF];
Caldwell & Bradley, 2001);Parental depression and anxiety (Depression, Anxiety and Stress Scale – Short Form [DASS-SF]: parent report;
Lovibond & Lovibond, 1995);Parental alcohol and drug use (CAGE and the Drug Abuse Screening Test - 10 [DAST-10]: parent reports;
Ewing, 1984;
Skinner, 1982); andChild welfare reports of CM and out-of-home placements, assessed by records within the collaborating sites.

Demographic and background information on families and children will be collected by means of a Profile Questionnaire. Details on socioeconomic status (SES), and risk of CM, will be collated from questions on, for example, parental age, health, marital status, education and employment, living circumstances, child health, and so forth. Data for all outcomes will be collected at baseline, 6- and 12-month follow ups by a researcher who will meet with the participant in the family home, or, if preferred, in a local family/health care centre.

***Process evaluation.*** The process evaluation will utilize a range of qualitative and quantitative measures to assess programme fidelity and implementation, recruitment of sites and families, participant engagement and experiences, and the feasibility of implementing the programme within child and family services in Ireland not involved in the trial (
Table 2). Fidelity and implementation will be assessed with: weekly session checklists of all key components; practitioner capacity to engage parents (Work Alliance Inventory short form;
Hatcher & Gillaspy, 2006); site and practitioner capacity to implement the programme with integrity (adapted version of the IY Agency Administration Implementation Effectiveness Questionnaire;
Webster-Stratton, 2014); and in-depth semi-structured interviews with practitioners and managers following programme delivery. Records of meetings, training, certification and receipt of supervision will also be documented.

Parental engagement and experiences will be assessed using: attendance records; parental feedback on key intervention components (e.g. the Incredible Years Parent Satisfaction Questionnaire); the Work Alliance Inventory short form that measures a participant’s experience of the practitioner (
Hatcher & Gillaspy, 2006); and an in-depth semi-structured interview with a purposive sample of participating parents (n = 15; selected based on site and demographic characteristics, including those who dropped out from the intervention). Brief interviews will also be conducted with children aged 7–11 years at baseline and 6-month follow up in order to assess the impact of the programme on their perceptions of family relationships and their own wellbeing. The child measures include: the Draw and Tell technique (
Merriman & Guerin, 2007), Cantril’s My Life Ladder (
Cantril, 1965) and My Family and Me (
Hill *et al.*, 1996).

We will also conduct interviews/focus groups with a range of child and family services nationally (n = 30 organisations) in order to investigate the feasibility of implementing the ChARM programme within current systems of care in Ireland. This is important in light of the difficulties experienced in retaining collaborating sites as part of the RCT.

Interviews will be conducted in the participants’ home/place of work or a local health care centre. Participants can elect whether to participate in an individual interview or a focus group. Written informed consent will be requested. Interviews will be audio-recorded (with participants’ consent) and will last no more than one hour with parents and service providers, and no more than 30 minutes with children. The parent of the child will be approached to seek their consent for their child to participate in the study and we will also seek the child’s written and verbal assent. To reduce participant burden, interviews with parents and children will be conducted at a different time from the administration of the measures for the impact evaluation.

***Costs analyses.*** In order to estimate the costs per family of delivering the ChARM programme, comprehensive cost diaries will be completed by sites (practitioners and managers) during and following the implementation process. Costs will be collected on: costs of training and supervision, staff time and materials involved in preparation, recruitment of families, intervention delivery, managerial overheads, referrals, and so forth. Parents (n = 50) will also complete a Services Utilization Questionnaire (SUQ) at baseline and 6-month follow up in order to record all health, educational and social services used by the family in the previous six months. The SUQ is based on an adaptation of the Client Service Receipt Interview (
Beecham & Knapp, 1992).

### Data analysis

***RCT.*** Changes in continuous primary and secondary outcomes at baseline and at six-month follow-up will be compared for the intervention and control groups using ANCOVA, controlling for intervention status, site, baseline score and any other baseline differences identified. Mean difference effect sizes, 95% confidence intervals (CIs), and p values will be reported for continuous outcomes. Changes at 12-month follow up will be conducted using ANOVA. Changes between study arms in categorical variables (i.e. data records of incidences of CM and out-of-home placements) at baseline and six-month follow up will be analysed using the Chi Square test of independence, reporting relative risk, 95% CIs and p values. Descriptive statistical summaries (e.g. means, standard deviations, frequencies) will be presented for primary and secondary outcome measures at each time point. All data for primary and secondary outcomes will be analysed using an intention-to-treat analysis, using multiple imputation (MI) to compensate for missing data at different assessment points. Imputation assumptions for MI will be reported and justified, and imputed data analysed as part of a sensitivity analysis. Parallel per protocol analyses will also be conducted for outcomes. Attrition analyses will be conducted at each time point to assess for differences between those who dropped out from the programme me and those who stayed. This will be based on an examination of key baseline variables (e.g. intervention arm, participant SES and wellbeing, child gender) and qualitative data outlining reasons for attrition.

Multiple regression techniques will be used to explore moderators of intervention effects (if present). Moderators will include: severity of risk and CM at baseline (measured using below and above clinical cut-off scores on the BCAPI, CTSPC, as well as frequency of CM incidences within substantiated reports); age and SES of parents and children (measured using a composite risk factor score derived from demographic data on the Profile Questionnaire); gender of child; parental mental health and problem substance use (using above or below clinical scores on the DASS, CAGE and DAST). Statistical analyses will be conducted using SPSS and Stata. We are aware of the possibility of low statistical power given that our numbers are lower than desired. Hence these analyses will be more exploratory in nature.

***Process evaluation.*** Quantitative assessments of programme fidelity and participant engagement/satisfaction will be assessed using descriptive statistics and using correlational and regression techniques, where necessary. Interview data will be fully transcribed and coded using the qualitative analysis software package MaxQDA (
MaxQDA, 2016). Key themes and subthemes will be identified using framework analysis, a method suitable for applied policy research that has specific questions, a limited period, a pre-designed sample and a priori issues (
Ritchie & Lewis, 2003). Analysis of themes will be informed by the MRC framework, and will identify programme and implementation processes, contextual factors, mechanisms of impact, and intended outcomes (
Moore *et al.*, 2014). Framework analysis uses five steps to identify themes: familiarization; identifying a thematic framework; indexing; charting; and mapping and interpretation (
Ritchie & Lewis, 2003).

For the child measures, drawings will be analysed using Visual Content Analysis (VCA), which is a technique for systematically describing written, spoken or visual communication (
Bell, 2001). Analysis of the drawings will involve coding for common themes/categories, such as who is present in the picture (peers, family, friends, or pets); the setting (such as watching TV or playing outside); use of colour; and facial expressions (e.g. happy or sad). Data from the VCA will be supported by data from the audio-recordings used in each child interview in order to thematically analyse the child’s perception of their life and family relationships.

***Economic evaluation.*** A societal perspective (public sector perspective and individual costs incurred by participants in attending the intervention) will be taken in the economic analysis. The CEA will be calculated through a three-step process. Firstly, the costs diaries will estimate the cost per family of delivering the programme. Unit costs of health and social care services used by families (e.g. GP, nursing, hospital visits) will be obtained from official government documentation, official government pay scales, the Casemix/HIPE unit of the Health Service Executive and any other relevant sources and/or agencies. Thirdly, a CEA will calculate an incremental cost-effectiveness ratio (ICER) to give the cost of obtaining a one-unit decrease on the two primary outcome measures (CTSPC-SF and SDQ) when comparing the ChARM programme to usual services at six-month follow up.

The ICER will use a 1000 replication bootstrap to provide a 95% CI accompanied by appropriate sensitivity analyses. Such sensitivity analyses may include how the ICER may vary according to the severity of the presenting problem at baseline or, for example, excluding non-recurrent costs (e.g. training, materials). The ICER accommodates sampling (or stochastic) uncertainty and varying levels of willingness to pay for reductions in the primary outcomes of interest.

A CBA will also be conducted to investigate the down-stream impact of the intervention on later costs, such as generating savings in relation to reduction in child welfare services, foster and residential placements, health and mental health service utilization, crime, education and unemployment. To conduct the CBA, the results of the CEA will be combined with estimates of the effects of CM on key outcomes in adult life. The effects of CM on adult outcomes can be assessed using secondary data sources and a monetary value will be assigned to the associated gains/losses of programme me delivery. The CBA will calculate an ‘internal rate of return’ to assess the desirability of investment in the programme. The ‘internal rate of return’ refers to the discount rate at which the value of the stream of future benefits exactly equals the initial cost of the programme, yielding a net present value equal to zero.

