## Abstract

The prevention of child abuse and neglect is a global public health priority due to its serious, long-lasting effects on personal, social, and economic outcomes. The Children At Risk Model (ChARM) is a wraparound-inspired intervention that coordinates evidence-based parenting- and home-visiting programmes, along with community-based supports, in order to address the multiple and complex needs of families at risk of child abuse or neglect. This paper presents the protocol for a study that will be carried out to evaluate this new service model (i.e. no results available as yet). The study comprises a multi-centre, randomised controlled trial, with embedded economic and process evaluations. The study will be conducted in two child-welfare agencies within socially disadvantaged settings in Ireland. Families with children aged 3-11 years who are at risk of maltreatment (n = 50) will be randomised to either the 20-week ChARM programme (n = 25) or to standard care (n = 25) using a 1:1 allocation ratio. The primary outcomes are incidences of child maltreatment and child behaviour and wellbeing. Secondary outcomes include quality of parent-child relationships, parental stress, mental health, substance use, recorded incidences of substantiated abuse, and out-of-home placements. Assessments will take place at pre-intervention, and at 6- and 12-month follow-up periods. The study is the first evaluation of a wraparound-inspired intervention, incorporating evidence-based programmes, designed to prevent child abuse and neglect within high risk families where children are still living in the home. The findings will offer a unique contribution to the development, implementation and evaluation of effective interventions in the prevention of child abuse and neglect.

The trial is registered with the International Standard Randomised Controlled Trial Number Register (DOI 10.1186/ISRCTN13644600, Date of registration: 3
^rd^ June 2015).

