***Exclusion criteria***

Families who display unstable substance use/mental illness.Parents who have had previous exposure to an evidence-based parent-training programme.Child is living in temporary or permanent out-of-home placement.

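### The chi-square test with a relative risk at baseline and six months does not measure change in recorded maltreatment and placement, adds an uninformative baseline test, ignores site, and is fragile if events are rare

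*Protocol article*

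**What the plan says.** The Data analysis section (RCT) names the target as "Changes between study arms in categorical variables (i.e. data records of incidences of CM and out-of-home placements) at baseline and six-month follow up" and says these outcomes "will be analysed using the Chi Square test of independence, reporting relative risk, 95% CIs and p values". Continuous outcomes are treated differently in the same paragraph: they get ANCOVA with site and baseline score as covariates.

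Both recorded outcomes are secondary. Table 1 takes them from site records with a six-month look-back; for maltreatment the entry reads "Social work record of incidence of child maltreatment in previous six months". The Exclusion criteria list "Child is living in temporary or permanent out-of-home placement". The Inclusion criteria admit families in which some maltreatment is already known to have occurred. Randomisation is stratified by site and follows the baseline assessment (Randomisation and blinding). The planned arms are "ChARM programme (n = 25) or to standard care (n = 25) using a 1:1 allocation ratio". No event rate is given for either outcome.

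**The concern.** The article itself fixes the test, the effect measure and the two time points, so this is more than a detail left to an analysis plan. Four things do not fit together.

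- A test of independence on a 2×2 table compares arm proportions at one time. Run twice, it gives two cross-sectional comparisons and no analysis of change.
- The baseline comparison comes before randomisation and says nothing about the programme.
- For placement, the eligibility rule almost empties the baseline table.
- Site is a stratification factor and enters the ANCOVA, but not this analysis.

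Separately, a relative risk is a fragile summary at 25 per arm. If events turn out to be few, the only test of the secondary hypothesis on substantiated abuse and placements could end without a usable ratio and interval.

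**Working it through.** **Inputs.** Arms of 25 and 25 (Abstract). Two-sided 5% level, assumed from the 95% intervals. Event rates are assumptions, shown over a range, because the article gives none. The article has no power or sample-size figure for these outcomes to reproduce.

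**1. Baseline placement.** A child in placement at entry is ineligible. With a six-month look-back, only a child who was placed and had returned home before entry could count. With no events in either arm, the relative risk is 0/0 and the chi-square statistic cannot be computed.

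**2. Zero events in an arm, equal rates.** For event rate p and n per arm:

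- P(control arm has none) = (1 − p)^n. The relative risk is then infinite or 0/0.
- P(at least one arm has none) = 1 − [1 − (1 − p)^n]². No finite log-scale interval exists.

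For p = 0.05 and n = 25: 0.95^25 = 0.277, and 1 − (1 − 0.277)² = 0.478.

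| Rate in both arms | Control arm has none | At least one arm has none |
|---|---|---|
| 1% | 78% | 95% |
| 2% | 60% | 84% |
| 5% | 28% | 48% |
| 10% | 7.2% | 13.8% |
| 15% | 1.7% | 3.4% |
| 20% | 0.4% | 0.8% |

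**3. Unequal rates.** If the programme lowers the rate, the chance that at least one arm has none is 1 − [1 − (1 − p₁)^25][1 − (1 − p₂)^25]:

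- 5% vs 2.5%: 66%
- 10% vs 5%: 33%
- 20% vs 10%: 7.5%
- 20% vs 5%: 28%

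**4. Expected counts.** With equal arms, each arm's expected event count is half the total, so it is below 5 whenever there are fewer than 10 events in all. At 25 per arm with equal rates, the smallest expected cell is below 5 in about 100% of tables at a 5% rate, 97.5% at 10%, 79% at 15%, 44% at 20% and 4% at 30%.

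**5. Size of the test.** Summing binomial probabilities over all tables at 25 per arm, the uncorrected chi-square test at nominal 5% has size 2.0% at a 5% rate, 4.9% at 10%, 5.5% at 20%, and at most 6.5% at any rate.

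**6. Would an exact test be better?** Power at 25 per arm, by the same enumeration:

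| Control vs programme | Chi-square | Fisher |
|---|---|---|
| 10% vs 5% | 8.1% | 1.3% |
| 20% vs 10% | 17.4% | 8.6% |
| 20% vs 5% | 38.2% | 19.8% |
| 40% vs 20% | 35.2% | 23.1% |

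For 20% vs 5%, Boschloo's test has 27%. At a 5% rate in both arms, Fisher's size is 0.08% against 2.0% for the chi-square test.

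**7. The score method.** At a difference of zero, the unstratified Miettinen-Nurminen statistic is the chi-square statistic times (N − 1)/N = 49/50. In the enumeration it had the same power as the chi-square test in all four rows of step 6. The site-stratified version was not enumerated.

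**The case against.** The strongest reply is that rarity is assumed. Known maltreatment makes a family eligible, so recorded maltreatment over six months may be common, and at 15% or more in both arms the zero-event problem almost disappears. That stands. A reader might infer that the relative risk will usually be undefined for both outcomes; the article does not support this. A zero in the programme arm alone also gives a relative risk of 0, which is defined; only its log-scale interval fails.

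A reader might also infer that small expected counts produce false positives. They do not at low rates, where the test is conservative, and its size never exceeds 6.5%.

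Nor are these the only outcomes free of unblinded parent report. HOME-SF is an observation, and the SDQ has a child version. The importance of the point cannot rest on that.

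Applying the planned 30% attrition would leave 25 × 0.7 = 17.5, about 18 per arm, and raise the chance of an empty arm to 64% at a 5% rate and 28% at 10%. But the article states that attrition for the primary measures, "factoring in 30 per cent attrition, we would need to recruit 150 families to detect a 0.8 effect size on our primary outcome measures", and site records need not be lost when a family misses an interview. I do not rely on these figures.

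Finally, zero-cell rules are commonly left to an analysis plan, and the word *changes* may be loose drafting, since the ANCOVA sentence uses it too. The lack of a zero-cell rule is therefore not the finding. What remains is that the article commits to a test, a measure and a baseline comparison that do not fit the stated target.

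**Conclusion.** The point holds in a limited form. Without any assumed event rate: the test is cross-sectional and does not measure change, the baseline test shows only chance imbalance and is nearly empty for placement, and site is ignored. Conditional on rare events, plausible for placement and less so for recorded maltreatment: at 25 per arm with equal rates, the relative risk or its interval fails in 48% of trials at 5% and 14% at 10%, but in 3.4% or less at 15% and above. If the programme works, failure is more likely than the control rate alone suggests (33% for 10% vs 5%).

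A reader might go further and call the six-month comparison invalid. It is not: it remains a proper randomised comparison, and leaving out site does not invalidate it. Severity is modest. The outcomes are secondary, the article calls the trial exploratory, and it concedes "We are aware of the possibility of low statistical power given that our numbers are lower than desired".

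**What to change.** Reword the sentence so that each recorded outcome is compared between arms at six months only, counting events in the six months since baseline.

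- Report the risk difference with a score interval stratified by site, such as Miettinen-Nurminen. It exists when an arm has no events.
- Give the relative risk only when both arms have events.
- Drop the baseline test and tabulate baseline frequencies.
- Take the p value from the same score method. If an exact test is wanted, use Boschloo's and state its power cost (27% against 38% for 20% vs 5%). Do not substitute Fisher's test (20%).

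The cost is a sentence or two of wording, a less familiar effect measure and slightly more analysis work. No new data are needed. The change does not cure low power; it ensures that an estimate with an interval can be reported however few the events.

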Schneider-Muñoz *et al.*, 2015). By contrast, a randomised controlled trial of WA versus standard services for maltreated children within those still living in the home and in out-of-home placements reported no differences in child and carer wellbeing (
Browne *et al.*, 2014). It has been noted that, while WA improves placement stability and is perceived as being a highly transportable and acceptable approach to working with families within current care systems, it tends to have less support than evidence-based programmes (EBPs) in improving clinical outcomes (
Bernstein *et al.*, 2015). Conversely, EBPs may lack feasibility and generalizability (
Bruns *et al.*, 2014). There is increasing recognition, therefore, that a WA approach, or indeed an approach inspired by wraparound principles, that incorporates evidence-based CM prevention programmes, while also coordinating other tailored community-based supports, may offer a useful model of care in enhancing both clinical outcomes and programme feasibility (
Bernstein *et al.*, 2015).

Evidence from meta-reviews has indicated that, of available EBPs, home visiting and group-based parent training programmes appear most successful in improving risk factors associated with CM, and to a far lesser extent, in reducing incidences of CM (
MacMillan & Wathen, 2014;
Mikton & Butchart, 2009). Nevertheless, there is little evidence to suggest that these stand-alone parenting programmes are sufficient in preventing CM in more high risk, disadvantaged families. For example, many ‘real world’ implementation studies have shown that less than 30–50 per cent of vulnerable families will attend a centre-based parenting programme and that more than half of these will drop out during delivery (
Axford *et al.*, 2012;
Furlong & McGilloway, 2015). Such failure to engage parents is unsurprising because, arguably, stand-alone parent programmes are typically not equipped to address the multiple and complex needs of families at risk of CM, which as outlined earlier, include addiction and mental health problems, housing and financial concerns, and so forth. Home-visiting interventions, on the other hand, appear to have more capacity than parenting programmes to engage with vulnerable families due to meeting within the family home and addressing other material and support needs besides coaching of parenting skills (
Macdonald *et al*., 2010).

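### A per-protocol analysis based on attendance would be non-randomised and probably favour ChARM; a complier-average estimate is the better secondary analysis

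*Protocol article*

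**What the plan says.** The protocol article (Data analysis, RCT) makes intention-to-treat the main approach: "All data for primary and secondary outcomes will be analysed using an intention-to-treat analysis", with multiple imputation for missing data. Continuous outcomes go into an ANCOVA "controlling for intervention status, site, baseline score and any other baseline differences identified". One further sentence adds: "Parallel per protocol analyses will also be conducted for outcomes". The article does not describe the per-protocol set, and it mentions no analysis of the effect of receiving the programme that keeps the randomised comparison.

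Other sections bear on how that sentence would work in practice:
- **Abstract:** families "will be randomised to either the 20-week ChARM programme (n = 25) or to standard care (n = 25) using a 1:1 allocation ratio".
- **Study design and Services as usual:** controls are offered ChARM only at T2, the six-month primary endpoint.
- **Table 2:** the process evaluation collects, from practitioners, "Records of parental attendance to program".
- **Home visits and Additional supports:** the number of home visits and the type and frequency of other supports are documented. Visits vary with family need, and some precede the group sessions.
- **Contamination:** staff are separated by arm, but leakage of ChARM content to controls is treated as possible and would be handled with a covariate.
- **Discussion:** even the most promising existing interventions are said not to engage the families at highest risk.

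**The concern.** Adherence to ChARM can be observed in one arm only. If the per-protocol set is built on attendance, families who attend little leave the ChARM arm, while the control families who would have attended little stay in. The two groups then differ in more than treatment, and no choice of attendance threshold restores the balance that randomisation gave.

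The article gives some reason to expect a direction. The Discussion says the families most at risk are hard to engage, and the description of the Positive Life Skills Programme links mental health and addiction problems to difficulty in engaging. If non-attenders have the worse prognosis, removing them from one arm flatters ChARM.

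The trial is small: 50 families, where the article's own calculation said it would "need to recruit 150 families to detect a 0.8 effect size on our primary outcome measures". An imprecise intention-to-treat result set beside a more favourable per-protocol result invites weight on the second. The attendance data needed for a better-founded estimate are already being collected.

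**Working it through.** The plan gives no figure on this point to reproduce. The size has to be explored under assumptions.

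**Inputs**
- From the article: 25 families per arm; ANCOVA with baseline score; no ChARM for controls before T2.
- Assumed: correlation r = 0.5 between baseline and outcome; share completing π = 0.7 or 0.5; correlation ρ = 0.3 between engagement and the part of prognosis that baseline does not explain. The article gives none of these.
- Outcomes are scored so that negative means benefit.

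**1. Bias with no true effect.** If completers are the top fraction π on a normal engagement scale, and φ is the normal density at the cut, then

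bias = −ρ × √(1 − r²) × φ/π, with √(1 − 0.25) = 0.866.

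- π = 0.7: φ = 0.348, so −0.3 × 0.866 × 0.348/0.7 = −0.13 SD.
- π = 0.5: φ = 0.399, so −0.3 × 0.866 × 0.399/0.5 = −0.21 SD.

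**2. Simulation** (25 per arm, ANCOVA, nominal two-sided 5%, 8,000 trials per setting):

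| π | ρ | Per-protocol estimate | Per-protocol false positives | ITT false positives |
|---|---|---|---|---|
| 0.7 | 0.3 | −0.13 SD | about 8% | about 5% |
| 0.5 | 0.3 | −0.20 SD | about 10% | about 5% |
| 0.5 | −0.3 | +0.21 SD | about 10%, nearly all towards harm | about 5% |

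The last row shows that the sign follows the assumed link between engagement and prognosis.

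**3. Cross-check without baseline adjustment.** Here the bias is (1 − π) × Δ, where Δ is the untreated difference between adherers and non-adherers. With Δ = 0.5 SD in favour of adherers it is 0.3 × 0.5 = 0.15 SD at π = 0.7 and 0.5 × 0.5 = 0.25 SD at π = 0.5, with 7.3% and 10.2% false positives. With Δ = 0 it is zero.

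**4. The alternative.** The complier-average estimate is the ITT difference divided by π.
- With no true effect it centres on zero.
- With a true effect of −0.5 SD in attenders and none in non-attenders (π = 0.5, ρ = 0.3), its median is −0.50, against −0.71 for per-protocol.
- Its standard error at π = 0.5 is about 0.52 to 0.54, against 0.30 for per-protocol: a ratio of 1.7 to 1.8. At π = 0.7 it is about 0.37 against 0.27.

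**5. Where the alternative fails.** If families below the attendance threshold still gain 0.2 SD, for example from home visits, the complier-average estimate is too large by (1 − π) × 0.2/π.
- π = 0.5: 0.5 × 0.2/0.5 = 0.20 SD, so about −0.70 instead of −0.50. That is no better than per-protocol.
- π = 0.7: 0.3 × 0.2/0.7 = 0.09 SD.

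**The case against.** **The comparison is inferred.** A reader might take the article to state that attenders will be compared with all controls. It does not. Defining a per-protocol set is commonly left to the analysis plan, which is not shown, so the missing definition is no fault. A per-protocol set could also exclude ineligible families or contaminated controls, in either arm. This stands, and the point is therefore conditional on an attendance-based set. That is still the natural reading, because controls have no programme to adhere to before T2.

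**The attendance rates belong to other programmes.** The introduction cites studies in which "less than 30–50 per cent of vulnerable families will attend a centre-based parenting programme and that more than half of these will drop out". A reader might apply these rates to ChARM. They describe stand-alone centre-based programmes, and the article cites them as a reason for building ChARM differently. Families here must be willing and able to attend and must agree to all three core components. The only loss figure planned for this trial, "factoring in 30 per cent attrition", is not a completion rate. This stands, so 70% completing is shown beside 50%.

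**The direction is not certain.** Home visits rise with need, so families receiving more may be worse off, and adjustment for further baseline differences could remove some of the bias. This stands too: bias towards benefit is probable, not established.

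**The remedy has assumptions of its own.** A reader might think that a complier-average estimate is simply unbiased. It is not if partial attenders benefit, or if controls receive ChARM content. This shapes the fix but does not remove the case for it.

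**Intention-to-treat leads.** Attrition analyses will also compare programme dropouts with stayers, and the article asks for caution in interpretation. These points limit the consequence. They do not make the per-protocol comparison randomised.

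**Conclusion.** The point holds in conditional form. An attendance-based per-protocol analysis would leave the randomised comparison whatever threshold is chosen, and it is open to selection bias, probably in favour of ChARM. At 25 per arm with no true effect, an engagement–prognosis correlation of 0.3 and a baseline correlation of 0.5, the bias is about −0.13 SD with about 8% false positives at 70% completing, and about −0.2 SD with about 10% at 50%. These values are assumptions: the bias vanishes if engagement is unrelated to prognosis and reverses if attenders are the worse-off families.

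The documents do not support saying that the planned analysis certainly exaggerates benefit, or that the trial's main conclusion is affected, because intention-to-treat covers all primary and secondary outcomes. This is a worthwhile and cheap improvement to a secondary analysis.

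**What to change.** - Keep intention-to-treat as the main analysis.
- For the effect of receiving ChARM, specify a complier-average estimate as the secondary analysis: two-stage least squares with randomised arm as instrument, recorded participation as exposure, and site and baseline score as covariates.
- Define exposure as any engagement, or as a dose, and count home visits as well as the 18 group sessions (4 Positive Life Skills plus 14 Incredible Years). A high session threshold would breach the exclusion restriction if partial attenders benefit.
- State that assumption, and the assumption that controls receive no ChARM content. Report the contamination data beside the result.
- Label any per-protocol result supportive and non-randomised.

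The cost is one extra model on data already collected. The drawback is precision: at 50% completing the standard error is roughly 1.7 times that of the per-protocol estimate, so with 25 per arm the interval will be wide and should be presented as such.
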